### 3.5. Statistical modeling

Statistical methods will be based on the intention-to-treat principle (McCoy, 2017). Given the heterogeneity of the measures collected, data will be normalized before being analyzed and in case of high percentages of missing data, they will be subjected to multivariate imputation (Sterne et al., 2009). The statistical analysis will be as follow:

–Descriptive statistics (median, interquartile range, mean, standard deviation, and absolute and percentage frequencies) will be applied to describe the sample characteristics and data.–Data distribution, assessed with the Shapiro–Wilk test, and appropriate correlation tests (i.e., Spearman’s rho, Pearson’s *r*, Cramér’s V, or point-biserial correlation coefficient) will be performed to study the presence of associations between the variables (collinearity).–Data grouping. Patients will be divided in two categories (i.e., *Responders* and *Non-Responders*) according to responsiveness to therapy, defined as an improvement of 5 points relative to the minimally clinically important difference (MCID) of the primary outcome measure (i.e., FMA-UE) (Page et al., 2012). To assess whether there is a statistically significant difference in the dose of therapy between the Responder and Non-Responder patient groups, Student’s *t*-test for unpaired data or Mann–Whitney test for each clinical variable will be performed, depending on distribution properties, as already proposed in previous studies (Salvalaggio et al., 2023). Then, with the aim to identifying the best set of variables (regressors) that can predict UL motor recovery in patients, appropriate regression models will be estimated. This step will be preceded by the evaluation of the requirements of the chosen model and by considering possible adjustments for mediating, moderating, and confounding factors. Prior to model fitting, preliminary diagnostic check will be made [i.e., variance inflation factor (VIF) for the study of collinearity independence among predictors]. Selection of the best set of regressors will be made taking into account appropriate indices. A diagnostic analysis (goodness-of-fit) of the model will be performed on the model to verify its assumptions and the fit to the available data. The statistical significance level will be set at *p* < 0.05, and all statistical analyses will be performed using the latest version of R software (R Core Team, 2022).

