#### 3.2.2. Sample size calculation

The sample size was calculated with regard to the main motor outcome assessing UL function (Fugl-Meyer Assessment for Upper Extremity – FMA-UE). From published data on the same cohort study design of stroke survivors admitted at the IRCCS San Camillo Hospital (Salvalaggio et al., 2023), and undergoing the same rehabilitative treatments described in this protocol, is expected that UL function improves with moderate standardized effect (Cohen’s *d* = 0.45), according to FMA-UE. Assuming an equivalent effect size *f* = 0.225, for repeated measures, within factors multivariate analysis of variance (MANOVA) design (Chen and Chen, 2010), in one group with two measurements correlating 0.5, given α = 0.05 and 1-β = 0.90, a total recruitment of 54 consecutive subjects would be needed. Considering a drop-out rate of 40%, a final number of 75 patients will be considered sufficient to conclude the study.

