#### 3.2.4. Clinical motor profiling of recruited patients

Each participant recruited for the present study undergoes a detailed clinical assessment including: (1) collection of patient medical history and records; and (2) use of validated outcome measures for quantifying stroke severity, functional, and sensorimotor impairments.

The following outcome measures are used for quantifying the severity of stroke sequelae:

–National Institutes of Health Stroke Scale (NIHSS) (Page et al., 2012) is a 42-points scale for quantification of stroke severity.–Oxfordshire Community Stroke Project (OCSP) (Bamford et al., 1991) is a clinical classification system for ischemic stroke, allowing to predict the site involved by the brain infarct.–Functional Independence Measure (FIM) (Granger et al., 1986) is a 126-points scale for measuring the level of independence in activities of daily living (ADLs).

Following is the list of validated outcome measures for profiling UL sensorimotor impairments:

–Fugl-Meyer Assessment for Upper Extremity (FMA-UE) (Fugl-Meyer et al., 1975) is a 66-points scale for profiling UL impairment by quantifying performance of complex and segmental voluntary movements, grasping, and coordination. We will also the sensation and pain/range of motion domains of the FMA, with a total score obtainable of 0–24 and 0–48, respectively.–Action Research Arm Test (ARAT) (Carroll, 1965) is a 57-points ordinal scale quantifying hand and arm activities.–Medical Research Council (MRC) muscle strength scale (Compston, 2010) is a 5-points ordinal scale for assessment of voluntary force, applied to shoulder abduction (SA) and fingers extension (FE).–Reaching Performance Scale (RPS) (Levin et al., 2004) is a 36-points scale for assessment of voluntary UL reaching task.–Box and Blocks Test (BBT) (Mathiowetz et al., 1985a) is a 1-min test for assessment of gross manual dexterity.–Nine Hole Pegboard Test (NHPT) (Mathiowetz et al., 1985b) is a 50-s test for assessment of fine finger dexterity.–Trunk Control Test (TCT) (Collin and Wade, 1990) is a 100-points outcome measure for assessment of trunk control.–Modified Ashworth Scale (MAS) (Bohannon and Smith, 1987) is an ordinal scale for assessment of muscle spasticity.

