#### 3.2.7. Quantification of rehabilitation intervention

Dose of therapy will be quantified both as the number of technological devices used for patient treatment (OT included) and dose (i.e., total number of hours) of intervention provided during the period of hospitalization. For the following analyses, dose of therapy is coded in terms of (i) total hours of rehabilitation specific for UL (i.e., UL technologies and plus OT), (ii) total hours of rehabilitation non-specific for UL (i.e., technologies for LL), and (iii) total amount of rehabilitation (i.e., hours of CT, and plus specific and non-specific UL interventions).

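### Section 3.5 tests dose of therapy against a 5-point Responder split of FMA-UE; that test keeps at most about 64% of the information in the continuous score

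*Protocol article*

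**What the plan says.** Section 3.5 forms two groups from the primary outcome: "Patients will be divided in two categories (i.e., *Responders* and *Non-Responders*) according to responsiveness to therapy, defined as an improvement of 5 points". The sentence ties the threshold to a published minimally clinically important difference (MCID), so the cut is prespecified and is not taken from the data.

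The groups are then used for the dose question: "To assess whether there is a statistically significant difference in the dose of therapy between the Responder and Non-Responder patient groups", a "test for unpaired data or Mann–Whitney test for each clinical variable will be performed", depending on the distribution.

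Both variables are numeric before the cut. Section 3.2.4 says that FMA-UE "is a 66-points scale for profiling UL impairment", and section 3.2.3 has it assessed at T0 and T1. Section 3.2.7 records "dose (i.e., total number of hours) of intervention provided during the period of hospitalization". The sample size in section 3.2.2 also uses the continuous scale: it is "expected that UL function improves with moderate standardized effect (Cohen’s *d* = 0.45), according to FMA-UE".

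After the group comparison, section 3.5 moves to prediction. To find the variables "that can predict UL motor recovery in patients, appropriate regression models will be estimated". It does not say whether the outcome of those models is a score, a change or the Responder class.

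**The concern.** Cutting the change at 5 points treats a patient who gains 4 points like one who loses 4, and a patient who gains 5 like one who gains 30. Patients near the threshold are classified by a point or two on a 66-point scale. A test of dose against this split therefore uses less of the data than a test against the score itself.

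Dose matters in this study. Section 2 lists the optimal dosage of each modality among its aims, and the Introduction criticises earlier prediction work for ignoring dose. The group comparison is the only dose test that section 3.5 names explicitly. The cohort is small and was sized for the pre–post change, so no power is claimed for a between-group comparison of dose. A real relation between dose and recovery could be missed for a reason that the data already collected would avoid.

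**Working it through.** **1. The plan's own figure.** Inputs from section 3.2.2: f = 0.225 (d = 0.45), two measurements correlating 0.5, α = 0.05, power 0.90. The repeated-measures F test has noncentrality λ = f²·n·m/(1 − ρ). At n = 54 this is 0.225² × 54 × 2 / 0.5 = 10.9, and power is 0.901. The stated 54 reproduces, and it is the sample size for a two-sided paired comparison of the continuous score.

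**2. Cohort sizes used below.** 75 is the planned recruitment and 54 the stated requirement. 45 is what remains if the stated 40% drop out of 75 (75 × 0.60).

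**3. Information kept by the split.** Assume normal change, linearly related to dose. With a share p of Responders, the efficiency of testing dose against the split, relative to the continuous change, is φ(z_p)² / [p(1 − p)].

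| Responders / Non-Responders | Efficiency | Loss | Effective n from 75 / 54 / 45 |
|---|---|---|---|
| 50/50 | 0.637 (= 2/π, the maximum) | 36.3% | 47.7 / 34.4 / 28.6 |
| 40/60 or 60/40 | 0.622 | 37.8% | 46.6 / 33.6 / 28.0 |
| 30/70 or 70/30 | 0.576 | 42.4% | 43.2 / 31.1 / 25.9 |
| 20/80 or 80/20 | 0.490 | 51.0% | 36.7 / 26.5 / 22.0 |

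**4. Where the cut might fall.** The article gives no SD, so I assume 8 to 20 points. With a correlation of 0.5, SD(change) = SD × √[2(1 − 0.5)] = SD, so the expected mean change is 0.45 SD. Reading the rule as a gain of at least 5 on an integer score, the cut is c = (4.5 − 0.45·SD)/SD in SD units from the mean.
- SD 8: c = 0.11, 46% Responders, efficiency 0.634
- SD 10: c = 0, 50% Responders, efficiency 0.637
- SD 20: c = −0.23, 59% Responders, efficiency 0.625

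On these assumptions the split is close to even, which is the most favourable case in the table.

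**5. Power.** I simulated 20,000 bivariate normal samples per case, testing at two-sided 0.05. A Pearson test on continuous change is set against a t-test of dose by group. The dose–change correlation is not in the article; 0.3 and 0.4 are assumptions.

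| n | Correlation | Continuous | 50/50 split | 30% Responders |
|---|---|---|---|---|
| 45 | 0.3 | 53% | 36% | 33% |
| 45 | 0.4 | 80% | 59% | 54% |
| 54 | 0.3 | 61% | 42% | 39% |
| 54 | 0.4 | 87% | 67% | 63% |
| 75 | 0.3 | 75% | 55% | 51% |
| 75 | 0.4 | 95% | 81% | 77% |

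**6. The same loss as sample size.** By Fisher's z, n = [(1.96 + 0.84)/atanh(r)]² + 3. For r = 0.3 and 80% power, n = 85 with the continuous change. An even split weakens the correlation to 0.3 × √0.637 = 0.239, and n becomes 135.

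**The case against.** Four points can be made for the plan.

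- **The split serves a stated aim.** Section 2 wants to identify the best responders, and the Discussion wants markers that stratify patients by whether they exceed the MCID. The threshold is fixed in advance and clinically referenced. This stands: it is a good reason to keep the comparison, and the split should not be reduced to a descriptive table. It does not make the split the better main test of dose.
- **Dose is not confined to the group test.** A reader might infer that the split is the whole dose analysis. The documents do not support that. The Abstract's summary and the end of the Introduction make rehabilitation measures inputs to the predictive model, and section 3.2.7 codes dose as hours in three ways for later analyses. The group comparison is the only explicitly named dose test, but dose may enter the regressions too.
- **The prediction models may be continuous.** A reader might carry the 36% loss over to them. Section 3.5 leaves their outcome unstated, and section 3.4.1 speaks of the degree of recovery at T1, which suggests a graded measure. An article may leave that choice to a fuller plan, so no loss is established there.
- **The size rests on assumed inputs.** This is also correct. With all 75 patients and a correlation of 0.4, the split test still has 81% power. Marked skew in the change scores would alter the efficiency figures.

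**Conclusion.** The point holds for the Responder versus Non-Responder comparison of dose in section 3.5. Under roughly normal change, linear in dose, that test discards at least 36% of the information, and more as the split moves away from even. Across correlations of 0.3 to 0.4 and 45 to 75 patients, an even split costs about 14 to 21 percentage points of power. The responder share, the SD and the dose–change correlation are assumptions, because the article gives none of them.

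This is an avoidable inefficiency in one named analysis. It is not a contradiction in the plan, and it does not undermine the study's sample-size figure of 54, which was derived for a different comparison.

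**What to change.** In section 3.5, make the main dose analysis a regression of T1 FMA-UE on dose in hours, with T0 FMA-UE as covariate, using the dose codings of section 3.2.7. Keep the prespecified MCID comparison of Responders with Non-Responders as a secondary, clinically interpretable analysis.

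The cost is one additional model and a slightly less direct clinical reading of the main result. No new data, visits or patients are needed. The power figures above are for the unadjusted change score, so those for the T0-adjusted model may differ.

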Evidence suggests that spontaneous recovery expresses its maximum effect from 3 to 6 months (Bernhardt et al., 2017), nevertheless recent results demonstrated that rehabilitation interventions can promote clinically significant improvements of motor outcomes even after this sensitive window, especially if high dose of therapy is provided (Daly et al., 2019; Ward et al., 2019). Indeed, motor improvements in UL recovery were found to be achieved after 90–300 h of rehabilitation, even in the chronic phase (Daly et al., 2019; Ward et al., 2019). Moreover, data available in the literature also emphasize the importance of the so-called “active ingredients” of rehabilitation (i.e., the specific elements which are assumed to be responsible for the treatment effect), but which are often not defined, classified, or measured (Ward et al., 2019).

During motor performance, there is an integration between motor and cognitive components (Barrett and Muzaffar, 2014; D’Imperio et al., 2021). For example, the control of sensorimotor aspects of motor actions requires attentional and cognitive demands, especially when performing complex movements. Consequently, cognitive abilities, such as attention, may play a key role, particularly in individuals recovering from stroke, as suggested by several studies (McDowd et al., 2003; Krakauer, 2006; Shafizadeh et al., 2017; VanGilder et al., 2020). This indicates that the identification of cognitive skills capable of guiding and predicting motor recovery could help in “*a priori*” patients stratification based on different recovery potentials.

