With regards to recovery prediction, data from the literature suggest that specific algorithms can be used to provide an accurate prediction of UL functional recovery. These algorithms are mostly based on clinical, imaging (magnetic resonance imaging – MRI) and neurophysiological (MEPs, collected with transcranial magnetic stimulation – TMS) measures. However, the validity of such models has been investigated only with assessments performed within a time window from 2 to 11 days (i.e., 2, 3, 5, 9, and 11 days) and UL prediction recovery at 3 months (Stinear, 2017). Moreover, factors such as: (i) variability in time of patient transfer to rehabilitation facilities, (ii) absence or delay in the acquisition of timely specific information (i.e., MEPs, FA, and National Institute of Health Stroke Scale – NIHSS), and (iii) different phases of recovery (i.e., subacute and chronic) when patients join the rehabilitation care, represent some of the most common confounders that can severely affect the predictive accuracy of the algorithms (Smania et al., 2009; Stinear, 2010, 2017; Stinear et al., 2012, 2017a). If only clinical outcome measures are available, predicting the effect of true recovery due to “treatment” over time is virtually impossible. Indeed, standalone clinical measures do not allow the thorough interpretation of the mechanisms underlying UL functional recovery (Stinear et al., 2007). For these reasons, imaging and physiological techniques, such as functional magnetic resonance imaging (fMRI) and TMS, have been previously used to accrue information on motor-related brain regions functionality following stroke recovery (Allman et al., 2016; Smith and Stinear, 2016). Similarly, diffusion tensor imaging (DTI) technique can be used to determine the anatomo-histological integrity of motor-related white matter (WM) pathways (Stinear et al., 2007). Recent preliminary studies have also suggested that measuring plasma levels of specific miRNAs (small RNA molecules that act as regulators of cell development, proliferation, cycling, and differentiation), and determining the specific genetic profile of stroke patients could provide useful biologically derived predictive markers of functional recovery (Chang et al., 2016; Edwardson et al., 2018; Dimyan et al., 2022).

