## 2. Objectives

The overarching objective of this project is to identify a set of variables, from a wide range of assessment modalities, which can reliably predict UL motor recovery after stroke, in patients undergoing rehabilitation in a clinical setting. This will help us to: (i) examine clinical features (e.g., behavioral, physiological, neural, and biological) associated with rehabilitation-induced recovery for identifying best responders to UL behavioral intervention, for rehabilitation after stroke, (ii) understand which modalities are the most suitable for a specific patient and the respective optimal dosage, and (iii) establish most effective times from onset of the acute event for modalities referral.

The richness of data acquired will also contribute to add new evidence on the predictive value of some emerging motor features (e.g., SAFE), biological markers (e.g., miR-941 levels), or physiological measures (e.g., EEG aperiodic parameters), described in greater detail in section “3. Materials and methods,” with the potential of being translated into current clinical practice.

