### 3.2. Participants’ recruitment and study design

#### 3.2.1. Participants

Study participants are recruited among stroke survivors admitted to a period of intensive neurorehabilitation treatment at the IRCCS San Camillo Hospital in Venice, Italy.

Inclusion criteria are: (1) age ≥18 years old; and (2) first ever cortical-subcortical, supratentorial ischemic or hemorrhagic, unilateral stroke, based on medical records.

Exclusion criteria are: (1) bilateral or pure cerebellar lesion; (2) presence of non-stabilized fractures; (3) diagnosis of other neurological and/or psychiatric disorder; (4) unstable medical condition (e.g., heart failure, untreated seizures, and psychiatric comorbidities); (5) any other relevant UL musculoskeletal impairment both before and after stroke, hampering assessment; and (6) inability to provide informed consent. Specific inclusion criteria for imaging analyses are (1) distinguishable lesion in FLAIR and (2) unilateral hemisphere lesion, while exclusion criteria are (1) bilateral lesion and (2) non-distinguishable lesion in FLAIR.

Specific exclusion criteria related to the instrumental technology (i.e., EEG, MRI, and TMS) employed in this project will be detailed in each specific section.

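### The 5-point responder label and the unadjusted dose comparison cannot separate response to therapy from spontaneous recovery

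*Protocol article*

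**What the plan says.** Section 3.5 (Statistical modeling) sorts patients into Responders and Non-Responders "according to responsiveness to therapy, defined as an improvement of 5 points" on the FMA-UE. It then tests for a "statistically significant difference in the dose of therapy between the Responder and Non-Responder patient groups", using an unpaired t-test or a Mann–Whitney test. Regression modelling follows, preceded by "considering possible adjustments for mediating, moderating, and confounding factors". Those factors are not named.

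Section 3.2.1 admits adults with a "first ever cortical-subcortical, supratentorial ischemic or hemorrhagic, unilateral stroke, based on medical records" and sets no limit on time since the event. Under section 3.2.3 every participant is treated to an individual plan for at least four weeks, eight on average, with T1 before discharge. There is no comparison group. Section 3.2.7 measures dose as hours accumulated over the stay.

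The Introduction reports that "spontaneous recovery expresses its maximum effect from 3 to 6 months". On the accuracy of existing prediction algorithms, it says that "different phases of recovery (i.e., subacute and chronic) when patients join the rehabilitation care, represent some of the most common confounders". It also distinguishes prognostic factors, which concern spontaneous recovery, from predictive factors, which concern response to an intervention. Section 2 nevertheless aims to identify the best responders and to "establish most effective times from onset of the acute event for modalities referral".

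**The concern.** Two stated choices are at issue.

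**The label.** A raw gain of 5 points between T0 and T1 is the sum of whatever therapy did, whatever would have happened anyway, and measurement noise. With no untreated or differently treated group, nothing in the definition separates these parts. By the article's own distinction, the groups describe improvement. They do not describe response to an intervention.

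**The dose test.** A two-sample test has no place for a covariate. If patients seen earlier after stroke both recover more on their own and receive more hours, Responders will show a higher dose even if therapy does nothing. Dose is not allocated independently of the patient: section 3.2.3 tailors treatment to need and ability.

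At stake is whether a dose difference, or a marker said to identify responders, is read as evidence about rehabilitation when it may reflect the time at which the patient was admitted.

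**Working it through.** **1. The plan's own figure.** The article gives no figure for this point. Its sample size (section 3.2.2) supplies the group sizes used below. With f = 0.225, two measurements and correlation 0.5, the noncentrality is λ = f²·N·m/(1−ρ) = 0.225² × 54 × 2/0.5 = 10.9 on (1, 53) degrees of freedom. Power is 0.901 at N = 54 and 0.895 at N = 53, so 54 reproduces. I use N = 54 and the recruitment target of 75.

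**2. What the label captures when therapy does nothing.** The documents give no SD of FMA-UE change and no spontaneous gain, so both are assumed. With normal gains of mean m and SD s, the share labelled Responder is 1 − Φ((5 − m)/s).

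| Mean spontaneous gain (points) | s = 4 | s = 6 | s = 8 |
|---|---|---|---|
| 0 | 11% | 20% | 27% |
| 4 | 40% | 43% | 45% |
| 8 | 77% | 69% | 65% |

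For example, with m = 8 and s = 6, 1 − Φ(−0.5) = 69%. With no therapy effect at all, the share of Responders runs from 11% to 77%, depending on spontaneous gain and spread.

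**3. What the dose test does when therapy does nothing.** All inputs are assumptions:
- half the cohort is subacute and half chronic;
- chronic patients have a mean gain of 0, subacute patients of 4 or 8 points;
- the SD of change is 6;
- dose has mean 60 h and SD 20 h within phase, with subacute patients receiving 0, 10 or 20 h more.

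There were 4,000 runs per setting. The Monte Carlo standard error near 5% is √(0.05 × 0.95/4000) ≈ 0.3 percentage points. The adjusted analysis regresses dose on responder group and phase.

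| Subacute gain | Extra hours | Unadjusted, N = 54 | Unadjusted, N = 75 | Adjusted, N = 54 | Adjusted, N = 75 |
|---|---|---|---|---|---|
| 4 | 0 | 4.6% | 5.2% | 4.8% | 5.1% |
| 4 | 10 | 8.1% | 8.3% | 5.8% | 5.5% |
| 4 | 20 | 12.3% | 15.8% | 4.8% | 4.5% |
| 8 | 0 | 5.5% | 5.2% | 5.1% | 5.3% |
| 8 | 10 | 13.2% | 18.3% | 4.6% | 5.8% |
| 8 | 20 | 36.9% | 48.6% | 5.1% | 5.3% |

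Without a dose–phase link there is no inflation. With one, rejection rises with the spontaneous gain, the link and the sample size. Adjustment for phase restores the nominal level.

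**4. A second route, through length of stay.** This is not in the simulation. Section 3.3.1 sets conventional therapy at no less than 1 h a day, 5 days a week. Over 4 weeks that is at least 1 × 5 × 4 = 20 h, and over 8 weeks 1 × 5 × 8 = 40 h. T1 falls before discharge, so a longer stay brings both more hours and more elapsed time in which to recover. The unadjusted test on total hours cannot tell these apart.

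**The case against.** **Covariates belong to the SAP.** A condensed article need not list them. The regression step allows adjustment for confounders, the Introduction names phase as one, and objective (iii) needs time from onset. This stands: the absence of a covariate list is not a finding. It does not reach the label or the two-sample dose tests, which section 3.5 states outright.

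**The open entry window is deliberate.** This also stands. Objective (iii) requires patients at varied times from onset, so the missing time limit is no defect in itself.

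**The main aim is prediction.** Section 2 seeks variables that predict recovery in patients undergoing rehabilitation. A marker that works partly through time since stroke is still a valid predictor for that aim. A reader might infer that such markers would be false positives. Assuming a time–gain correlation of 0.5 and marker–time correlations of 0.3 to 0.6 would give significance in 19% to 60% of studies of 54 patients. The documents do not support that reading. The correlations are not in them, the plan is multivariable, and the association would be a true one. It misleads only if it is reported as response to therapy.

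**Section 4 concedes the limit.** It speaks of candidate prognostic factors, says that the lack of controls limits causal reading, and looks to external validation, possibly in a randomised trial. That is a partial answer. The same section still offers the Responder split as a basis for stratifying patients and personalising treatment, and it changes nothing in the analysis.

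**Conclusion.** The point holds for the label and for the dose comparison. That the label cannot separate spontaneous gain from therapy response follows from the design and needs no assumed numbers. The bias in the dose test is conditional: about 5% rejection if dose is unrelated to phase, 8% to 18% under the intermediate assumptions (10 extra hours), and up to 37% to 49% if subacute patients gain 8 points on their own and receive 20 h more. Case mix, SD of change, spontaneous gain and dose–phase link are all assumed.

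A reader might conclude that the study will report spontaneous recovery as a treatment effect. The documents do not establish that. They do not show how dose relates to phase, and the later regression may well include time from onset. What they establish is that the stated label and the stated dose tests offer no protection against it. This should be changed, and it can be changed before analysis without altering recruitment or care.

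**What to change.** 1. **Dose analysis.** Replace or supplement the two-sample tests with a regression of FMA-UE gain (or of the 5-point split) on dose, adjusted for time from stroke to T0 and for T0 FMA-UE. For total hours, a sensitivity analysis adding the T0–T1 interval would address length of stay, although hours and interval may be strongly correlated.
2. **Claims about markers.** Where a marker is said to predict response to rehabilitation, always retain time since stroke in the model. Models meant purely for prediction need not force it. Splitting every result into early and late strata is not advised with 54 to 75 patients.
3. **Label.** Name the groups 'improved by at least 5 points' and 'not improved', and drop the wording that ties the split to therapy.
4. **Objectives (i)–(iii).** State them as associations with recovery under usual rehabilitation, in line with the limitation in section 4.

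The cost is some rewording and one or two model degrees of freedom; the date of onset should be in the medical record. Adjustment removes measured confounding by phase but cannot attribute an individual's gain to therapy without controls. The relabelling is therefore needed as well, and the claim becomes more modest.

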**Methods/design:**

A total of 75 stroke patients, admitted at the IRCCS San Camillo rehabilitation Hospital in Venice (Italy), will be included in this study. Here, we describe the rehabilitation programs, clinical, neuropsychological, and physiological/imaging [including electroencephalography (EEG), transcranial magnetic stimulation (TMS), and magnetic resonance imaging (MRI) techniques] protocols set up for this study. Blood collection for the characterization of predictive biological biomarkers will also be taken. Measures derived from data acquired will be used as candidate predictors of motor recovery.

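### The responder split is a cut of T1 minus T0 FMA-UE and baseline FMA-UE is not a required covariate, so baseline severity and scales that track it can appear to predict response through coupling

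*Protocol article*

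**What the plan says.** All references are to the protocol article.

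- **Response.** Section 3.5 gives the only operational definition of response: "defined as an improvement of 5 points relative to the minimally clinically important difference (MCID) of the primary outcome measure". This is a gain from T0 to T1, cut at 5 points.
- **Two-group tests.** The opening of the sentence gives their purpose as comparing the dose of therapy between the groups. It then says that "Student’s *t*-test for unpaired data or Mann–Whitney test for each clinical variable will be performed".
- **Regressions.** The section continues: "with the aim to identifying the best set of variables (regressors) that can predict UL motor recovery in patients, appropriate regression models will be estimated". It does not say whether recovery means the gain, the T1 score or responder status.
- **Adjustment.** The model step is preceded "by considering possible adjustments for mediating, moderating, and confounding factors". T0 FMA-UE is not named.
- **Predictors.** The abstract says: "Measures derived from data acquired will be used as candidate predictors of motor recovery". Sections 3.2.3 and 3.2.4 show that these data include T0 FMA-UE and other scales of the same arm (ARAT, RPS, BBT, NHPT, MRC strength).
- **Purpose.** Section 2 seeks features "associated with rehabilitation-induced recovery for identifying best responders to UL behavioral intervention".
- **Planning correlation.** Section 3.2.2 sizes the study "in one group with two measurements correlating 0.5".

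**The concern.** When the outcome is built by subtracting T0, a T0 variable can be related to it without carrying any information about the T1 state beyond the T0 score. Patients with a low T0 score tend to gain more, partly through regression to the mean, and any scale that follows T0 inherits part of that relation. An unadjusted Responder versus Non-Responder test of such a scale then largely asks whether the scale is correlated with T0 FMA-UE.

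The study is meant to deliver a set of variables that identify responders to rehabilitation. Without T0 FMA-UE held fixed, that set may include measures that only restate initial severity, and a useful marker that also correlates with T0 may be weakened or masked. The planned collinearity check and selection of regressors could even drop T0 FMA-UE in favour of a collinear scale, because nothing protects it.

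**Working it through.** **Inputs from the article.** d = 0.45 (f = 0.225), T0-T1 correlation r = 0.5, α = 0.05, power 0.90, 54 patients before drop-out, 75 recruited, 40% drop-out (section 3.2.2); 5-point gain (section 3.5); FMA-UE maximum 66 (section 3.2.4).

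**Assumptions.** Bivariate normal scores; equal SDs at T0 and T1; SD 15 points (10 and 20 also tried); no ceiling in the simulation.

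**1. The plan's own figure.** For one group and two measurements, λ = n·2f²/(1−r) = 54 × 2 × 0.050625/0.5 = 10.94. This is a paired t-test with standardised gain 0.45 (54 × 0.45² = 10.94). Power is 0.901 at n = 54 and 0.895 at n = 53, so 54 reproduces.

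**2. Coupling with the gain.** With k = SD(T1)/SD(T0),

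corr(T0, T1−T0) = (rk − 1)/√(1 + k² − 2rk).

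At r = 0.5 and k = 1 this is −0.5/√1 = −0.50.

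**3. Coupling with the split.** At SD 15 the mean gain is 0.45 × 15 = 6.75 and the SD of the gain is 15 × √(2 × 0.5) = 15. The cut lies at (5 − 6.75)/15 = −0.117, which gives about 55% Responders. Dichotomising reduces −0.50 to about −0.40.

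**4. Rejection rates at n = 54, equal SDs, two-sided 0.05 (4,000 simulated studies per row).** The correlate has an assumed correlation of 0.6 with T0 FMA-UE and relates to T1 only through it.

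| r | corr(T0, gain) | T0 vs gain | T0 vs split | Correlate vs gain | Correlate vs split | Correlate vs T1, adjusted for T0 |
|---|---|---|---|---|---|---|
| 0.5 | −0.50 | 98% | 88% | 61% | 42% | 5.1% |
| 0.8 | −0.32 | 65% | 45% | 28% | 19% | 5.1% |
| 0.95 | −0.16 | 22% | 15% | 11% | 8% | 5.1% |

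Repeat runs of the r = 0.5 case gave 87% to 88% for T0 and 40% to 43% for the 0.6 correlate on the split. A correlate of 0.8 gave about 67%. Changing the assumed SD to 10 or 20 leaves the T0 rate at about 87%.

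**5. Other sample sizes, r = 0.5, on the split.** If 40% of 75 are lost, 75 × 0.6 = 45 remain: T0 81%, correlate 37%. With all 75: 96% and 55%.

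**6. Unequal SDs.** At r = 0.5, k = 1.2 gives −0.36, k = 1.4 gives −0.24 and k = 2 gives 0. At r = 0.7, k = 1.4 gives −0.02, with a rejection rate of about 5%. At r = 0.9, k = 1.2 gives +0.15.

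**7. A different kind of correlate.** Suppose the marker tracks a stable state that the FMA-UE measures with error at both visits. At r = 0.5 and n = 54 it is significant in 4.9% of studies against the gain, 4.8% against the split, and 50% against T1 adjusted for T0.

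**8. Ceiling, not included above.** Section 3.2.1 sets no FMA-UE entry limit. A patient at 62 or more at T0 can gain at most 66 − 62 = 4 points and is a Non-Responder by construction. This pushes in the same direction.

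**The case against.** - **The regression target is not stated to be the gain.** This stands. A reader might infer that recovery is T1 minus T0 throughout; the article uses the gain only for the split. Once T0 FMA-UE is in a linear model, regressing the gain or T1 on T0 and a marker gives the same coefficient and p-value for the marker. What matters for the regressions is therefore whether T0 is forced in.
- **The named aim of the two-group test is dose, which is not a T0 measure.** This also stands, although the sentence extends the test to each clinical variable. Dose has no built-in coupling. However, section 3.2.3 has treatment tailored to the patient, so if hours follow initial severity, dose becomes a correlate of T0 like any other.
- **Covariates are commonly left to a fuller plan.** True of the detail, but the gain-based split and the unadjusted tests are fixed in the article.
- **The aim is prediction, and an association between low T0 and a 5-point gain would recur in similar patients.** Correct. The percentages are rejection rates for a real association, and it would be wrong to read them as type I error. The difficulty is interpretation: the association would be presented as a marker of rehabilitation-induced recovery. Section 4 concedes a causal limit from the absence of controls, but does not address this.
- **Adjustment is not neutral.** The 50% in step 7 is real. For a prediction aim it is not a false positive, because such a marker does add information about T1 beyond an error-prone T0 score. It would be misleading if read as an effect on recovery.

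**Conclusion.** The point holds for the responder split and its unadjusted tests. For the regressions it is conditional, because their outcome and covariates are left open. At the planning correlation of 0.5, with equal SDs and 54 patients, T0 FMA-UE would separate the groups in about 88% of studies. A 0.6 correlate linked to T1 only through T0 would do so in about 40%.

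These sizes rest on r = 0.5, which is a power-calculation input and not an estimate for this cohort, and on equal SDs, which the article does not state. A higher correlation shrinks the effect, and a larger spread at T1 can remove or reverse it.

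A reader might infer that every clinical, TMS, EEG or MRI measure that correlates with severity will be flagged, by arithmetic alone and with a fixed sign. The article does not support that: a marker of a stable state is not coupled to the gain at all. The narrower point still warrants a change, since the baseline value is already collected and the adjustment is nearly free.

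**What to change.** In section 3.5:

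1. State T1 FMA-UE as the outcome of the prediction models, with T0 FMA-UE forced into every model and exempt from collinearity-based or other selection.
2. If Responder status is kept, analyse it by logistic regression with T0 FMA-UE forced in, including for the dose comparison, in place of the unadjusted t or Mann-Whitney tests. The simulation covered the linear model; the same reasoning applies here, because a measure linked to T1 only through T0 is independent of responder status once T0 is held fixed.
3. Judge every other T0 variable by what it adds to the model containing T0 FMA-UE.
4. State that the association of T0 FMA-UE with its own change will not be reported as a predictor of rehabilitation-induced recovery.

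**Cost.** Some wording and one degree of freedom; both FMA-UE scores are already collected. Fewer variables will be significant, and scales that duplicate T0 FMA-UE will tend to drop out. A marker of a stable state may remain significant after adjustment, so results should be described as added prediction and not as a causal effect on recovery.
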